### Sample size

The recruitment target for the overall RCT is n = 100 participants (n = 20 from each of the five participating centres). From the pilot study data [41], the sample size of n = 100 (n = 25 in each of the four study arms) would give 80% power at a significance level of 0.05 to detect a difference of 1.1 between the IAH scores (assessed using the Gold Score) of the 50 participants randomised to either of the CSII arms and the 50 randomised to either of the MDI arms. A difference of at least one point (on the 7-point scale) is considered to be a clinically relevant change on the Gold Score. The calculation is based on the use of the 2-sample t-test and the assumption, taken from the pilot data, that the standard deviation of the IAH score is 2 (mean ± SD Gold Score in the pilot study was 2.57 ± 1.90 in the CSII arm and 4.0 ± 1.79 in the MDI arm).

### Outcomes / statistical analysis

The principal analysis will examine the factorial structure of the treatment and monitoring regimen effects on the difference in IAH (Gold score) at 24 weeks using analysis of covariance (ANCOVA). Baseline IAH (Gold score) and stratification (centre and baseline HbA1c) variables will be included among the covariates to be considered in addition to suitable summaries of questionnaire scores and glucose monitoring data collected at baseline prior to randomisation. The glucose monitoring data to be collected include time spent for the following separate ranges: <2.5 mmol/l, <3 mmol/l, <4 mmol/l, >7 mmol/l, >10 mmol/l, between 4 and 7 mmol/l and between 3 and 10 mmol/l. The inclusion of baseline HbA1c as a covariate will enable the examination of possible interactions between effects observed and these values.

Further analyses will be undertaken concerning IAH to corroborate the Gold Score; the Gold Score will be compared with scale and subscale scores derived from the Clarke Questionnaire and the Hypoglycaemia Awareness Questionnaire (HypoA-Q) at 24 weeks.

These measures will also be subject to analysis as for the primary outcome. Additionally, a binary indicator of IAH response (defined as a Gold Score of <4 or ≥4) at 24 weeks will be analysed using logistic regression making use of the covariates used for the primary outcome analysis.

There will also be an additional analysis of the (paired) change in IAH (Gold Score) over the 24-week duration of the trial using the t-test without consideration of the intervention or monitoring groups in order to evaluate the effect of undergoing any intervention or monitoring over the 24-week period.

Other outcomes will be assessed at baseline and 24 weeks. Analysis methods will generally be similar to that described for the primary analysis but alternative techniques such as McNemar’s test and logistic regression will be used as appropriate.

Further analyses will be undertaken using HbA1c and the separate continuous glucose monitoring measures (time spent in the following separate ranges: <2.5 mmol/l, <3 mmol/l, <4 mmol/l, >7 mmol/l, >10 mmol/l, between 4 and 7 mmol/l and between 3 and 10 mmol/l) as outcome variables.

Similar analyses will be undertaken on scores from all PRO measure scores used in the study (Table 2).

A number of measures relating to SH (ADA criteria) will be analysed: number of episodes of SH at 24 weeks, change in SH between baseline and 24 weeks (reported as difference in annualised rate pre and post-intervention), change in SH between baseline and 24 weeks (reported as the proportion of participants with reduction in number of SH events compared between the timepoints) and change in proportion without SH between baseline and 24 weeks.

Changes in weight, total daily dose of insulin, and in glucose lability will be subject to analysis in a similar manner to the primary outcome.

Wherever possible participants who elect to withdraw from the study will be followed up so that final outcome data are obtained, enabling their inclusion in an Intention to Treat (ITT) analyses. This will form the analysis groups for the analyses described above.

Analyses restricted to those participants who were allocated to use RT-CGM will be considered, in order to allow use of the further covariate of low or high CGM use (defined by consideration of a pre-defined cut-off value) throughout the 24-week period. Variables analysed in this manner will include IAH (Gold Score), episodes of SH, HbA1c and several of the glucose monitoring measures.

Variables with missing data will be examined and the amount of missing data described. Data analysis will take the form of a complete case analysis, although imputation of values may be considered for the primary outcome variable alone should this be missing to a sufficient extent.

Significance levels will be set at α=0.05 throughout.

Safety data are to be documented but will not be subject to statistical analysis.

A detailed analysis plan will be finalised prior to the commencement of data analysis.

Data from the clamp study will be analysed separately; however a comparison will be made between the IAH (Gold) based definition of response and a response measure derived from the clamp results.

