### Participants

Participants will be recruited from the diabetes clinics of the five participating UK tertiary referral and academic hypoglycaemia/CSII centres (Royal Bournemouth Hospital, Bournemouth; Addenbrooke’s Hospital, Cambridge; Newcastle Diabetes Centre, Newcastle upon Tyne, UK; Derriford Hospital, Plymouth; Northern General Hospital, Sheffield). Patients with T1DM, a history of IAH and increased risk of SH will be assessed to determine if they are eligible for the study. It is envisaged that the majority of these will have experienced SH within the preceding year, although this is not mandatory for study participation. Those who are considered potentially eligible will be approached to give their written informed consent before attending for a screening visit at which inclusion criteria will be checked.

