### Four week baseline period

After consent, participants will undertake a 4-week wash-in period before the 24-week RCT period. Participants will be educated in the use of the study-specific prospective SMBG hypoglycaemia diary. All participants will be provided with a study hand-held glucometer (Contour link®, Bayer Healthcare) to measure daily 4-point and weekly 8-point profiles. They will be asked to record clinical details of all glucose levels <4 mmol/l and symptomatic hypoglycaemic events. All participants will wear a blinded CGM device (iPro™ 1, Medtronic) for 7 days during the baseline period.

At the end of the wash-in period, participants will attend for a baseline study visit where the investigator will complete the GCP-compliant baseline Case Report Form (CRF). This will record demographic information, full diabetes-specific clinical history including frequency and consequences of SH events over the preceding 12 months and full clinical examination assessing complication status. The study SMBG / hypoglycaemia diary will be collected and CGM device downloaded. In addition, hypoglycaemia awareness will be re-evaluated using the validated Gold Score [11] and Clarke questionnaire [42].

A first morning urine sample for albumin: creatinine ratio will be collected together with dilated retinal photography if not performed within the preceding 6 months. A blood sample will be taken for HbA1c (DCCT-aligned), urea and electrolytes, liver function tests and lipid profile analysed at local site quality-assured clinical laboratory. Study-specific PRO questionnaire booklets will be completed comprising several validated and novel measures. During design of and preparation for the study, new measures were developed by the team to capture aspects of participant experience for which validated measures did not exist (e.g. hypoglycaemia cues) or where there was specific concern that existing measures were insensitive (e.g. the Gold and the Clarke have been demonstrated to lack sensitivity to improvements in awareness). All PRO measures included in the evaluation are listed in Table 2.

**Table 2 T2:** Validated and novel patient reported outcome measures assessed during the Hypo COMPaSS trial

**Validated PRO measures**	**Novel PRO measures undergoing validation**
• The Gold Score [44]	• The Hypoglycaemia Awareness Questionnaire (HypoA-Q)*
• The Edinburgh Hypoglycaemia Survey [54]	• The Hypoglycaemia Burden Questionnaire (HypoB-Q)* – part A only

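### Two of the three severe-hypoglycaemia change measures are not adjusted for length of observation; read as written, they set a 12-month baseline count against a 24-week count and show a fall when nothing has changed

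*Protocol article*

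**What the plan says.** The Outcomes / statistical analysis section names four SH quantities. One is an on-trial count, "number of episodes of SH at 24 weeks". The other three are changes from baseline to 24 weeks:

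1. a change "reported as difference in annualised rate pre and post-intervention";
2. a change "reported as the proportion of participants with reduction in number of SH events compared between the timepoints";
3. the "change in proportion without SH between baseline and 24 weeks".

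The baseline SH record is described under Four week baseline period. The baseline case report form takes the "frequency and consequences of SH events over the preceding 12 months". Table 1 places a detailed SH history at visit 3 and again at later visits. No pre-trial window of 24 weeks is mentioned anywhere.

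Prior SH is expected but not required: "the majority of these will have experienced SH within the preceding year, although this is not mandatory for study participation".

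For outcomes other than the primary, the section says "Other outcomes will be assessed at baseline and 24 weeks", with McNemar's test and logistic regression available where suitable, and "Significance levels will be set at α=0.05 throughout".

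**The concern.** A count over 52 weeks will usually exceed a count over 24 weeks in the same person at the same underlying rate, and a person is more likely to be event-free over the shorter period. Annualising removes this from the first measure. The second and third are worded as a raw count and a raw event-free proportion, so nothing removes it there.

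The stake is the before/after statement. Reducing the risk of recurrent SH is part of the stated primary objective, and the Discussion expects definitive evidence that recurrent SH can be prevented. There is no education-only or untreated arm, so an overall claim of prevention has to lean on change from baseline. Two of the three listed change measures would lean towards benefit for a reason unrelated to treatment.

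**Working it through.** The article gives no expected value for these measures, so there is no figure of its own to reproduce.

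**Inputs from the article.** Baseline window 52 weeks (Four week baseline period); on-trial window 24 weeks, t = 24/52 = 0.4615 year; n = 100 (Sample size); α = 0.05, taken as two-sided.

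**Inputs assumed.** The SH rate m per person-year and its spread between people. Counts are Poisson, or Poisson with gamma-distributed personal rates of shape k (smaller k means more heterogeneity). Each person's rate is the same before and during the trial.

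**Expected events.** m × 0.4615 on trial against m × 1 at baseline: a ratio of 0.46, an apparent fall of 54%.

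**SH-free share over s years.** S(s) = exp(−ms), or (1 + ms/k)^(−k).

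**Fewer or more events.** Given N events over the combined 76 weeks, the baseline count is binomial with probability 52/76 = 0.684. Someone with a single event therefore looks improved with probability 68% and worse with probability 32%. Summing over N gives the columns below.

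| Assumed rate, unchanged | Fewer events | More events | SH-free, 12 months → 24 weeks |
|---|---|---|---|
| 0.742/yr, Poisson | 41.5% | 15.5% | 47.6% → 71.0% |
| 1/yr, Poisson | 48.1% | 16.7% | 36.8% → 63.0% |
| 2/yr, k = 1 | 51.4% | 13.3% | 33.3% → 52.0% |
| 2/yr, k = 0.5 | 43.6% | 10.7% | 44.7% → 59.3% |
| 4/yr, k = 1 | 63.9% | 12.1% | 20.0% → 35.1% |

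The first row is anchored on the pilot's 71% without recurrent SH over 6 months (Background), treated here as a 24-week share: m = −ln(0.71)/0.4615 = 0.742 and S(1) = exp(−0.742) = 0.476. Holding 71% and adding heterogeneity gives a 12-month SH-free share of 53%, 57% or 61% for k = 1, 0.5 or 0.25, so the spurious gain runs from 23 points down to 10.

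A second anchor is the 37% one-year SH prevalence in unselected type 1 diabetes (Background). The SH-free share moves from 63% to exp(−0.462 × 0.4615) = 81% (Poisson), or to 79%, 77% or 73% for k = 1, 0.5 or 0.25: a gain of 10 to 18 points.

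**Wider range.** Over 0.5 to 8 events per year (Poisson, k = 1, k = 0.5), 24 to 87% show fewer events against 8 to 17% more. The SH-free artefact nearly disappears at 8/yr with no heterogeneity (0.0% → 2.5%); the artefact in the reduction measure does not.

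**If McNemar's test were applied to SH-free status.** The discordant probabilities are S(t) − S(1 + t) for apparent improvement and S(1) − S(1 + t) for apparent worsening. For the first row S(1.4615) = 0.338, giving 0.710 − 0.338 = 0.372 against 0.476 − 0.338 = 0.138. With n = 100 the exact test rejects in about 90% of such null trials. On the 71% anchor with k = 1, 0.5 and 0.25 it rejects in 82%, 73% and 57%.

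**Equal 24-week windows, same assumptions.** Fewer and more events balance: 26% each (1/yr, Poisson), 27% each (2/yr, k = 1), 33% each (4/yr, k = 1). The SH-free share does not move, and the exact test rejects in about 3 to 4%.

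**Equal windows, restricted to people with a baseline event.** The balance is lost: 69% fewer against 6% more (1/yr, Poisson) and 56% against 21% (2/yr, k = 1). This is regression to the mean.

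**The case against.** The strongest reply is that the 12-month link is inferred. No sentence says that the second and third measures use the 12-month total. Annualising the first shows that the authors had exposure time in mind, the events in the detailed SH history might be dated, and the article promises a fuller analysis plan that could set a matched window. This stands as a limit on certainty. It does not remove the point, because the article fixes the measures and names one SH-specific baseline period, and taken together these give unequal windows. The 4-week wash-in diary would not help: against 24 weeks the artefact reverses (2/yr, k = 1: SH-free 87% → 52%).

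It is also fair that the anchors are loose. The 71% is a post-intervention figure from a 6-month pilot, and McNemar's test is offered for other outcomes generally rather than assigned to these measures. The rejection rates are therefore conditional illustrations.

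Three stronger readings are tempting but unsupported:

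- A reader might infer that the comparisons of CSII with MDI, or RT-CGM with SMBG, are biased. The windows are the same in every arm, so they are not tilted in this way.
- A reader might infer that including people with no baseline SH, who cannot show a reduction, inflates the benefit. It lowers the proportion with a reduction, so it works against showing benefit.
- A reader might treat this as undermining the trial's main result. The primary outcome is the Gold score, and the Discussion places SH events second.

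**Conclusion.** The point holds for two secondary before/after measures and should be fixed. Read as written, both compare 52 weeks with 24 weeks. With no change in SH rate, expected events drop to 46% of baseline. In the tabulated scenarios 42 to 64% of participants appear improved and 11 to 17% worse, and the SH-free share rises by about 10 to 26 points across the table and the two anchors. These sizes rest on assumed rates and heterogeneity. The direction does not, although the SH-free shift becomes small at very high, homogeneous rates. The conclusion also rests on the inference that the 12-month history is the baseline for both measures. The annualised rate, the on-trial count, the randomised contrasts and the Gold score analysis are unaffected.

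**What to change.** Define both measures on equal windows. At the visit 3 detailed SH history, record the number of SH events in the 24 weeks before baseline separately from the 12-month total, and compare all participants on that count with the 24-week on-trial count. State this window next to each measure.

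If the 24-week count cannot be obtained, replace the two measures with SH rates per person-year, from a count model with log exposure time as an offset.

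Do not restrict the reduction measure to participants with a baseline event. Report descriptively how many had none.

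The cost is one case report form field and a change of wording. The shorter window will contain fewer baseline events, and the reported change will be smaller. Equal windows remove only this artefact. Any regression to the mean from enrolling people at high risk remains, so causal statements should still rest on the randomised contrasts.

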### Intervention period

#### Randomisation

Participants will be allocated by third party concealed randomisation by centre and baseline HbA1c (with stratification cut-off of 64 mmol/mol (8%) to one of four groups for a period of 24 weeks):

MDI with SMBG (group 1; n = 25).

MDI with SMBG and RT-CGM (group 2; n = 25).

CSII with SMBG (group 3; n = 25).

CSII with SMBG and RT-CGM (group 4; n = 25).

As this is an open study it is not possible for participants to be blinded to study treatment arm. Randomisation will be administered centrally by Newcastle Clinical Trial Unit (NCTU) using a secure web based system.

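### Two of the three severe-hypoglycaemia change measures compare raw before and after counts over unequal windows, so they would show improvement when the event rate has not changed

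*Protocol article*

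**What the plan says.** Under Outcomes / statistical analysis, the Protocol article names four SH measures. The first is "number of episodes of SH at 24 weeks", which is not a change measure. The other three describe change from baseline to 24 weeks:

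- a difference in annualised rate before and after the intervention;
- change "reported as the proportion of participants with reduction in number of SH events compared between the timepoints";
- "change in proportion without SH between baseline and 24 weeks".

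Only the first of these three is put on a common time scale.

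That section gives no baseline window for any of them. Under Four week baseline period, the baseline case report form records "frequency and consequences of SH events over the preceding 12 months". The same section says that "participants will undertake a 4-week wash-in period before the 24-week RCT period", with a hypoglycaemia diary kept throughout. Under Randomisation, participants are allocated "to one of four groups for a period of 24 weeks". No section describes a 24-week SH count before randomisation.

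For outcomes other than the primary, the article says that methods will generally resemble the primary analysis, but that "alternative techniques such as McNemar’s test and logistic regression will be used as appropriate".

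**The concern.** A count depends on how long one counts. If a participant's SH rate stays the same, 24 weeks will usually hold fewer events than the preceding 12 months and is more likely to hold none. Both raw measures therefore drift towards improvement for a reason unrelated to treatment. Annualising the rate measure in the same sentence deals with this problem for that measure only.

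The before/after reading matters here. Reducing the risk of recurrent SH is part of the stated primary objective. The Background says that the trial dispenses with an education-alone arm, and the Discussion expects definitive evidence that recurrent SH is preventable. A claim about optimised management as a whole, across all four arms, has to rest largely on change from baseline.

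**Working it through.** The article gives no figure for the SH measures, so there is none to reproduce. The check asks what each measure would show if every participant kept the same SH rate throughout.

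**Inputs from the article.** Baseline window 12 months (52 weeks); trial window 24 weeks; n = 100; significance level 0.05.

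**Assumptions, not in the article.** Mean SH rate μ of 0.5 to 4 per person-year. Counts are Poisson, or gamma-Poisson with shape k = 1 or 0.5 to allow rates to differ between people.

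**Window ratio.** w = 24/52 = 0.4615; inverted, 52/24 = 2.17.

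**Proportion without SH over t years.** Poisson: exp(−μt). Gamma-Poisson: (1 + μt/k)^(−k).

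- μ = 1, Poisson: exp(−1) = 36.8% over 12 months; exp(−0.4615) = 63.0% over 24 weeks; spurious gain 26.2 points.
- μ = 1, k = 1: 1/2 = 50.0%; 1/1.4615 = 68.4%; gain 18.4 points.

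**Proportion with fewer or more events.** Given a person's rate, the two counts are independent Poisson variables with means μ and 0.4615μ. The probabilities that the second is below or above the first are summed over counts and averaged over the gamma distribution of rates.

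**Paired test.** For McNemar's test the discordant probabilities are b = P(SH before, none after) and c = P(none before, SH after). At μ = 1, Poisson, b = 0.632 × 0.630 = 0.398 and c = 0.368 × 0.370 = 0.136. With n = 100, the approximate rejection probability is Φ{[(b − c)√n − 1.96√(b + c)] / √[(b + c) − (b − c)²]} = Φ{(2.62 − 1.43)/0.68}, or about 96%.

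| μ per year | Counts | SH-free, 12 months → 24 weeks | Fewer / more events | Fewer / more, equal 24-week windows | McNemar rejects (approx.) |
|---|---|---|---|---|---|
| 0.5 | Poisson | 61% → 79% | 33% / 13% | 17% / 17% | 82% |
| 0.5 | k = 0.5 | 71% → 83% | 24% / 8% | 12% / 12% | 66% |
| 1 | Poisson | 37% → 63% | 48% / 17% | 26% / 26% | 96% |
| 1 | k = 1 | 50% → 68% | 39% / 13% | 20% / 20% | 87% |
| 2 | Poisson | 14% → 40% | 62% / 17% | 34% / 34% | 99% |
| 2 | k = 1 | 33% → 52% | 51% / 13% | 27% / 27% | 90% |
| 4 | Poisson | 2% → 16% | 75% / 13% | 39% / 39% | 93% |
| 4 | k = 0.5 | 33% → 46% | 54% / 10% | 28% / 28% | 76% |

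Over the whole grid the spurious gain in the SH-free proportion is 12 to 26 points. Simulating whole trials instead of using the approximation, McNemar's test rejects in 69% to 99% of null trials (uncorrected) or 59% to 99% (exact). With equal 24-week windows the figures are about 5% to 6% and 3% to 4%.

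**If baseline meant the 4-week diary.** At μ = 1, Poisson, the SH-free proportion goes from exp(−4/52) = 92.6% to 63.0%, a spurious fall of about 30 points. The windows are still unequal and the bias reverses.

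**Between arms.** Take μ = 2, k = 1 and a true rate ratio of 0.5. Among all participants, the proportion with fewer events differs between arms by 8.0 points with the 12-month baseline and by 9.6 points with equal windows.

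**The case against.** Four points on the other side have weight.

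- **The window is inferred.** The 12 months comes from the description of the case report form, and the statistics section fixes no baseline window. The article also defers detail to a later analysis plan. This limits how flatly the defect can be stated. But the measures are defined here, one is annualised and two are not, and neither baseline period that the article describes (12 months or 4 weeks) matches 24 weeks.
- **McNemar's test is not tied to SH.** It is one example for other outcomes, to be used where appropriate, and the pooled paired analysis is specified only for the Gold score. This stands, so the rejection rates are conditional on such a test being used. The shift in the measures themselves does not depend on the test.
- **Randomised comparisons are not biased.** A reader might infer that CSII versus MDI, or RT-CGM versus none, is distorted. The article does not support that: the windows are the same in every arm, so no false difference arises. The loss of contrast is also modest. It looks larger (12 points against 20) only among participants with SH at baseline, a restriction the article does not make.
- **SH is secondary.** The primary outcome and the sample size rest on the Gold score. The 24-week count and the annualised rate stand beside the two affected measures and do not share the fault.

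**Conclusion.** The point holds for the before/after reading of two secondary measures. As worded, with the only SH-count window the article states, both lean towards improvement when nothing has changed. The SH-free proportion gains about 12 to 26 points. A reduction appears in 23% to 75% of participants, against 8% to 17% with an increase. A paired test, if applied, would reject in about 60% to 99% of null trials.

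The direction follows from the window lengths alone. The size rests on assumed rates of 0.5 to 4 per person-year and on the assumed dispersion. Outside that range the artefact in the SH-free proportion can shrink: at 8 per year with pure Poisson counts the gain is only 2.5 points and the rejection rate about 34%.

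A reader might also conclude that a false finding is nearly certain or that the trial's main result is at risk. Neither follows: the rejection rate falls well short of certainty in the overdispersed cases, and no primary conclusion depends on these two measures. The point should be fixed because the trial's broader message about preventing recurrent SH would draw on them.

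**What to change.** Define both measures on equal windows: SH in the 24 weeks before the baseline visit against SH in the 24-week randomised period. The earlier count can be taken from the detailed SH history that Table 1 already schedules at visit 3. Where that history cannot be split by date, drop the before/after versions, compare the 24-week SH-free proportion between randomised arms, and keep the annualised rate for before/after change.

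Do not annualise the two binary measures. One event in 24 weeks becomes 2.17 per year and would count as an increase over one event in 12 months. A zero stays a zero after scaling, so the shorter window still yields more event-free people.

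The cost is one extra count on the baseline history form and a change of analysis wording. No visit, treatment or sample size changes. The downside is that fewer baseline events are counted, and some histories may not be dated finely enough.

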### Trial Governance

Trial management will be overseen by a Trial Management Group who will meet regularly to discuss the operational aspects of the trial. An independent Data Monitoring and Ethics Committee (DMEC) will be convened to undertake independent review, monitoring safety and efficacy endpoints. The DMEC will comprise two physicians not connected to the trial (at least one of whom will have expertise in hypoglycaemia), one statistician and one patient representative. The DMEC will have full access to unblinded study data.

A Trial Steering Committee (TSC) will supervise the trial, ensuring it is conducted to high standards in accordance with the protocol, the principles of GCP, and with regard to participant safety. This committee will have an independent chair with expertise in hypoglycaemia. In addition to the Chief Investigator ([name]) and Principal Investigators, the TSC will consist of a sponsor/funder representative, representatives of the Newcastle Clinical Trials Unit and two consumer representatives. The TSC will also consider safety issues for the trial and relevant information from other sources, ensuring at all times that ethical considerations are met when recommending the continuation of the trial.

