## Discussion

Over recent years, it has become increasingly clear that SH is the major factor limiting the overall level of glucose control achievable in those with established T1DM. We believe that this study will provide definitive evidence that recurrent SH is preventable even in the majority of those at highest risk. This will enable a truly evidence-based approach to improving day-to-day diabetes management for all those currently living with the risk and fear of SH. In addition, characteristics of the minority in whom optimised conventional therapy is likely to prove inadequate will be defined, enabling early identification and intervention.

While the interventions in this trial are widely used in an attempt to reduce the incidence of SH, there is little evidence from adequately powered RCTs supporting their use, with most existing RCTs having been powered for change in glycated haemoglobin rather than SH or IAH. The primary objective of this trial is to determine whether these treatments improve awareness of hypoglycaemia and, secondarily, to determine whether they have an impact on SH events and overall glycaemic control. Crucially, this unique trial will also determine the impact of these intensive interventions on a range of patient-reported outcomes.

The trial does pose challenges, perhaps foremost the need to ensure equal input to all study participants and not provide additional care to those randomised to pump therapy. The protocol was designed to take this into consideration. Participants randomised to MDI will also be provided with insulin pumps so that this group is not disadvantaged by not having access to a bolus calculator. Secondly, study investigators will need to remain absolutely focused on biochemical hypoglycaemia avoidance, undiluted by attempts to tighten or maintain overall glycaemic control. This may be made more challenging by existing investigator and participant behaviours. For this reason, detailed insulin titration protocols (detailed above) will be used across all sites.

This ambitious and intensive trial will demonstrate definitively whether SH, a cause of major morbidity in up to 5000 adults with T1DM in the UK, can be prevented successfully in even those at highest risk by optimised conventional management using existing technology. Overall biomedical, psychosocial and health utility impact of MDI, CSII and RT in this group will be determined employing optimised measures as detailed above.

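### Adverse events outside the analysed outcomes have no planned estimate or confidence interval by randomised factor

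*Protocol article*

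**What the plan says.** The rule is in the protocol article, Outcomes / statistical analysis: "Safety data are to be documented but will not be subject to statistical analysis". It carries no qualification, and the article does not define what counts as safety data.

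The same section commits to analysing several measures on which a treatment could do harm:

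- Severe hypoglycaemia: "A number of measures relating to SH (ADA criteria) will be analysed: number of episodes of SH at 24 weeks", followed by three measures of change from baseline.
- Glycaemia: "Further analyses will be undertaken using HbA1c and the separate continuous glucose monitoring measures". The CGM ranges include time below 2.5, 3 and 4 mmol/l and above 7 and 10 mmol/l.
- Metabolic effects: "Changes in weight, total daily dose of insulin, and in glucose lability will be subject to analysis", in the same way as the primary outcome.
- Other outcomes: "Analysis methods will generally be similar to that described for the primary analysis".

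The section also announces a detailed analysis plan, to be finalised before data analysis starts. Trial Governance gives an independent committee unblinded data for "monitoring safety and efficacy endpoints".

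**The concern.** Insulin route and real-time CGM are both randomised, so adverse events linked to either can be compared without confounding. Only the CSII groups deliver insulin through the pump, with infusion-set changes. Only the RT-CGM groups are encouraged to wear a real-time sensor continuously, and they continue with it for a further 18 months after the 24-week period.

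If the sentence is followed as written, events outside the listed outcomes would be recorded, but no difference between factor levels would be estimated and no limit put on it. In groups of 50, a list with few or no events is easily taken as evidence of safety when it excludes only fairly large risks. This is a choice that the article states. It is not a detail left open for the analysis plan, which would have to depart from the sentence in order to give between-group estimates.

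**Working it through.** **Step 1. What the sentence covers.**

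| Type of event or measure | Planned analysis by randomised factor |
|---|---|
| Severe hypoglycaemia | Yes, several measures |
| CGM low and high glucose, HbA1c | Yes, as outcome variables |
| Weight, insulin dose, glucose lability | Yes, like the primary outcome |
| Other adverse events (e.g. serious, device-related) | None; documented only |

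The gap is the last row.

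**Step 2. Group sizes and the plan's own figure.** Sample size gives 100 participants, 25 per arm, hence 50 v 50 for each factor. The only design figure is 80% power for a Gold score difference of 1.1 with SD 2 at 0.05 (taken as two-sided). With the normal approximation:

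- standard error = 2 × √(2/50) = 0.40
- 1.1 / 0.40 = 2.75, and 2.75 − 1.96 = 0.79
- power = Φ(0.79) = 78.5%

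The noncentral t gives 77.7%, and a detectable difference of 1.13 at 80% power, which rounds to 1.1. The figure reproduces to rounding. It matters here only because it fixes the 50 per factor level. The article states no figure for harms.

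**Step 3. What zero events would exclude.** The exact two-sided 95% upper limit for 0 events in n is 1 − 0.025^(1/n).

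- n = 50: 1 − 0.025^(1/50) = 7.1%
- n = 25: 1 − 0.025^(1/25) = 13.7%

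The one-sided 95% limit for n = 50 is 1 − 0.05^(1/50) = 5.8%.

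**Step 4. What an interval would show.** These are Newcombe 95% intervals for a risk difference at 50 v 50. The event counts are assumptions chosen to show the range.

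| Participants with an event | Difference (points) | 95% interval (points) |
|---|---|---|
| 0 v 0 | 0 | −7.1 to +7.1 |
| 2 v 0 | 4 | −3.7 to +13.5 |
| 5 v 2 | 6 | −5.0 to +17.7 |
| 10 v 5 | 10 | −4.3 to +24.2 |

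**Step 5. Would formal tests help?** The power of a two-sided 0.05 comparison of two proportions, 50 v 50, is Φ[(Δ − 1.96·√(2p̄(1−p̄)/50)) / √((p₁(1−p₁)+p₂(1−p₂))/50)], where Δ is the risk difference and p̄ the mean of the two risks.

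- 2% v 10%: (0.08 − 1.96 × 0.0475) / 0.0468 = −0.28, so power is 39%
- 5% v 15%: (0.10 − 1.96 × 0.0600) / 0.0592 = −0.30, so power is 38%

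Tests would miss most excesses of 8 to 10 points. Intervals show this limit openly.

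**The case against.** The strongest reply is that the harms most specific to this trial are analysed, and that the sentence only forgoes formal testing of the remainder. Documenting events does not rule out counts by arm, and the layout of adverse-event tables commonly belongs in the analysis plan. The insulins are used within licence and the monitors are CE-marked. Every participant receives the same pump and meter, and no stated objective concerns safety.

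Much of this stands. Forgoing tests is defensible on the power in Step 5, and counts by arm may well be produced. What remains is that the article excludes statistical analysis outright, and an interval or an upper limit falls within that term on an ordinary reading.

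A reader might infer three stronger points, which the article does not support:

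- **That harms in general go unestimated.** Step 1 shows otherwise.
- **That the Discussion is contradicted.** It says: "Overall biomedical, psychosocial and health utility impact of MDI, CSII and RT in this group will be determined employing optimised measures as detailed above". The closing words tie the promise to measures already listed, and safety is not named.
- **That committee monitoring of safety conflicts with the rule.** Oversight during the trial and estimation in the final report are different functions. The committee's review is a mitigation, although it puts no estimate in the report.

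**Conclusion.** The point holds as a minor reporting weakness. Adverse events not already analysed as outcomes have no planned estimate or interval by insulin delivery or monitoring. An empty list could then be over-read, since 0 of 50 leaves risks of up to 7.1% open and 0 of 25 risks of up to 13.7%.

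This assumes full groups of 50 and 25, and that the sentence is applied as written. The event counts are illustrative, and nothing in the article suggests that an imbalance is expected. The primary analysis, the sample size and the stated objectives are unaffected.

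**What to change.** Replace the sentence on safety data with wording such as:

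> Safety data are adverse events not already analysed as outcomes. Those recorded will be tabulated by insulin-delivery factor and by monitoring factor, showing participants with an event, number of events and person-time. Risk or rate differences will be given with 95% confidence intervals, and zero counts with an upper confidence limit. No hypothesis tests will be performed.

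The period should be stated for each factor. After 24 weeks insulin delivery returns to routine care and may change, whereas the RT-CGM comparison continues to 24 months.

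The cost is this short amendment and one table, drawn from events that are to be documented anyway. The article does not list which events are captured, so the table is limited to those recorded. The downside is wide intervals, as Step 4 shows.
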